#### Secondary research outcomes

Self-harm with and without intent to dieSelf-Injurious Thoughts and Behaviours Interview (SITBI) [28]: The SITBI comprises 74 questions and is widely used. There is acceptable evidence in support of its measurement properties in research [28].Suicidal thoughts and behavioursSuicidal Behaviours Questionnaire (SBQ-ASC) [29]: The SBQ-ASC will be used to identify participants’ suicidal thoughts and behaviours. It was developed through participatory methods with autistic adults. The measure has good content validity, structural validity, internal consistency, convergent and divergent validity, test–retest validity, sensitivity, and specificity for distinguishing those with or without lifetime experience of suicide attempt [29].Life disadvantagesVulnerability Experience Quotient (VEQ) [30]: The VEQ is a 60-item scale which has been developed through participatory methods with autistic adults to reflect adverse life experiences across 10 themes, such as childhood maltreatment, non-suicidal self-injury, bullying, and victimisation as a child or adult and discrimination.Health economicsEQ-5D-5L [31]: A standardized instrument used as a measure of health-related quality of life. The descriptive system comprises of five dimensions: mobility, self-care, usual activities, pain/discomfort, and anxiety/depression. Each dimension has a 5-level response scale, from “no problems” to “unable to” engage in the activity (mobility, self-care, usual activities) or “no” to “extreme” (pain and anxiety). The response statements are coded between one to five. The digits for the five dimensions can be combined into a 5-digit number that describes the participant’s health state.Bespoke Resource Utilisation Questionnaire: Provides information to capture the support services participants are accessing, that is, “usual care” derived from prior feasibility study work and existing tools (www.DIRUM.org).Bespoke Time and Travel Questionnaire: Provides information to capture travel time and costs related to contacts with healthcare providers derived from prior feasibility study work and existing tools (www.DIRUM.org).

### Suicide prevention intervention

The intervention will be AASPs, adapted in partnership with autistic people and those who support them, compared to usual care. AASP arm participants will still receive their usual care. Safety plans consist of a prioritized list of hierarchical steps that can be used prior to or during a crisis to mitigate risk of self-harm and suicidal behaviour [32]. They involve identification of (1) warning signs, (2) internal coping strategies, (3) social contacts and locations, (4) family members or friends that may offer help or (5) professionals or agencies to help, and (6) how to keep the environment safe. The safety plan can be personalised to the individual’s needs and have been shown to be efficacious in a range of clinical groups.

We have co-produced an AASP template for autistic adults which is available at https://sites.google.com/view/mentalhealthinautism/resources/safety-plan. Then, we engaged with autistic adults, family members of autistic adults, and service providers who support autistic people, where further adaptations were made to improve the accessibility, functionality, and overall experience of developing an AASP. The AASP is flexible (e.g. timing, method of delivery) and personalisable (e.g. colours and font). Adaptations included prompts with visually distinct key information, a section on “what is important to me” rather than “my reasons for living”, and explicitly considering how the individual communicates distress. The AASP also includes an optional resource kit, with tools to identify emotions, scales/pictorial representations, and suggested support services. Our public and patient involvement (PPI) with autistic people and those who support them has identified safety plans as a promising intervention to prevent self-harm and suicide in autistic adults. They are particularly suitable for autistic people due to the concrete steps involved in formulating the plan. Many autistic people do not realise they are in crisis until it is too late, and due to societal barriers and differences in communication style to non-autistic people, it can be difficult to seek help [33, 34]. AASPs may help autistic people identify warning signs of an approaching crisis and provide them with a personalised plan for seeking help. This is the first evaluation of AASPs.

The AASP will be completed with the support of a trained support worker or member of the research team (depending on participant preference and staff availability) in addition to usual care. The support worker may or may not be at a service the participant is already accessing, depending which organisations agree to take part in the study and which support services the autistic adult is accessing. The training was developed in partnership with autistic people and includes the service provider’s role in the study, information about suicide and self-harm in autistic people (including videos from autistic adults about their experiences with mental health), adaptations from standard safety planning, considerations when working with autistic people (e.g. double empathy problem; [35]), opportunities to discuss and practise the AASP, and feedback from people who have completed the AASP. The training is delivered by the research team.

### Strategies to maintain participation in the study

A number of strategies will be utilised to maintain participation in the study. Newsletters designed by researchers and an advisory committee of autistic adults, summarising the current progress of the study and any findings, will be sent to participants and service providers participating in the study. Similarly, cards will be sent to participants, thanking them for their involvement in the study, to encourage continued participation in the study. Additionally, in cases of nonresponses to researchers by participants, prompts via email, text, or call (depending on the participant’s communication preference) will be sent to encourage participation and minimise participant withdrawal. At baseline, contact information for a trusted person will be collected. They can be contacted in the case of nonresponse from a participant.

### Harm

Serious adverse events (SAEs) will be captured for participants from consent until the follow-up assessment at week 24. A SAE is any untoward medical occurrence in a participant that results in death, is life-threatening, requires inpatient hospitalisation, results in significant disability, and consists of congenital anomaly or other important medical event that jeopardises the participant. Occurrences do not have to be caused by or related to the study. Due to the nature of the study, it is likely that participants are at increased risk of self-harm and suicidal behaviour. We will not report repeated self-harm or suicidality unless it meets the above criteria. Serious adverse events are not anticipated in the study; therefore, any event will be classed as unexpected.

If a clear safeguarding concern arises, this will trigger an immediate response. We have considered potential issues related to safeguarding and have built in mitigation of these into the design. All research associates (RAs) and therapists will be fully trained and have enhanced DBS. A risk register will be developed to manage potential adverse events. A principal investigator (PI) will liaise with RAs to check for SAEs and will take appropriate action, and a chief investigator (CI) will immediately review SAEs in accordance with the trial risk assessment and protocol; both will use clinical judgement in assigning seriousness and causality of SAEs. If any such events are identified, they will be reported to the sponsor and to REC. All such events will be logged in a SAE form and recorded in a site file. If a participant is actively suicidal with imminent risk (e.g. a concrete plan), the RA will discuss with the participant and their CI/PI about the person’s suitability for the study and whether withdrawal is appropriate.

Additionally, researcher wellbeing is encouraged due to the sensitive nature of the study. Research staff have been advised to avoid carrying out sensitive tasks at times when regular support may not be available afterwards (e.g. Friday afternoons) and to schedule in “downtime” after completing potentially upsetting tasks. The research team will have regular informal and formal opportunities to debrief.

### Randomisation

Participants will be randomised on a 1:1 basis to receive either the AASP + usual care or usual care, without stratification. Randomisation occurs online through sealed envelope (https://www.sealedenvelope.com), facilitated by an unblinded RA who will inform participants of the outcome. Participants will be aware of their randomisation status due to the nature of the intervention.

### Procedure

The baseline measures will be completed before the participants are randomised to the treatment arms. For participants recruited to AASP + usual care who were recruited via non-NHS third sector organisations, a trained support worker from that organisation will complete the AASP with the participant; the participant can then use the AASP as required. Individuals who self-refer will either be paired with a trained support worker from one of the non-NHS third sector organisations or will complete the AASP with a member of the research team, based on their preference. With permission, we will record sessions during which the AASP is completed to enable us to determine fidelity. Based on feasibility study work, we anticipate that completion of the safety plan will take approximately 1 h. The support workers will inform the RAs at each site of the date of completion of the safety plan for each participant. Data consent, data collection, and the development of the AASP may take place remotely via telephone or video call.

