**Professionals only**				
Acceptability and feasibility semi-structured interview for professionals				X

^a^Demographics to include — socio-economic status, employment, housing, access to support, physical health, and education

^b^At baseline, this questionnaire asks about their entire life. At F1, it asks about the past month. At F2, it asks about the past 5 months

^c^Randomisation to take place following completion of baseline assessment

^d^Only completed by participants allocated to the AASP arm

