### Data collection and data management

Overall responsibility for data collection lies with the CI. Data collected on paper assessment tools will be entered onto a secure validated data management system at sites. A unique trial number is allocated at recruitment and will be used to identify participants on all paper assessment tools used throughout the duration of the study. No participant identifiable data will leave the study sites. The quality and retention of study data will be the responsibility of the CI. All study data will be retained in accordance with the latest directive on Good Clinical Practice (GCP; 2005/28/EC) and local policy. Staff involved in the conduct of the study, including PIs, Trial Management Group, and RAs, will have access to the site files. Clinical information shall not be released without the written permission of the participant, except as necessary for monitoring and auditing by the sponsor, its designee, regulatory authorities, or the research ethics committee. Secure anonymised electronic data will, however, be released to the research study analysts for analysis. The PI and site staff involved may not disclose of use for any purpose other than the performance of the study, any data, record, or other unpublished, confidential information disclosed to those individuals for the purpose of the study. Prior written agreement from the sponsor or its designee must be obtained for the disclosure of any said confidential information to other parties. Any requests to access the final trial dataset may be considered under the sponsor data-sharing policy.

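### The Randomisation and Procedure sections conflict on whether research associates (RAs) are masked: safety plan completion dates, which exist in one arm only, are not limited to the unblinded RA

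*Protocol article*

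**What the plan says.** All references are to the protocol article.

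- **Randomisation.** Participants are allocated to one of two arms: "Participants will be randomised on a 1:1 basis to receive either the AASP + usual care or usual care, without stratification". The online allocation is "facilitated by an unblinded RA who will inform participants of the outcome". Participants themselves are not masked: "Participants will be aware of their randomisation status due to the nature of the intervention". The adjective applied to this RA is the only reference in the article to the masking of staff.
- **Procedure.** "The support workers will inform the RAs at each site of the date of completion of the safety plan for each participant". A self-referred participant may instead have the plan delivered by the study's own staff: such a person "will complete the AASP with a member of the research team, based on their preference".
- **Suicide prevention intervention.** This section also allows either type of deliverer: "The AASP will be completed with the support of a trained support worker or member of the research team".
- **Data collection and data management.** "Staff involved in the conduct of the study, including PIs, Trial Management Group, and RAs, will have access to the site files". No restriction relating to allocation is given.
- **Table 1.** The SITBI is scheduled at baseline, 1 month and 6 months, and the SBQ-ASC at baseline and 6 months. The System Usability Scale (SUS) and Client Satisfaction Questionnaire (CSQ-8) are scheduled at 6 months, with the footnote "Only completed by participants allocated to the AASP arm". An acceptability and feasibility interview with autistic adults takes place at the same visit.
- **Aims.** Comparing outcome measures between the arms is listed as an addition to the feasibility aims.

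**The concern.** Calling one RA unblinded serves a purpose only if some other RAs are meant not to know the allocation. The Procedure section then sets up a routine message that carries the allocation and addresses it to the site RAs in general. One section implies a safeguard, and the next gives an instruction that, read plainly, breaches it.

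What is at stake is limited but real. The SITBI is administered as an interview about self-harm and suicidality, so an interviewer who knows the arm may probe or record differently. That could distort the between-arm comparison. The Design section also says that the pilot is to judge the suitability of processes for a definitive trial, including outcome measures and follow-up assessments. If routine messages reveal the arm, the pilot will say little about whether masked assessment is workable.

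**Working it through.** The article states no figure on this point, so the check is a reading of the sections side by side.

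1. **Does a completion date reveal the arm?** Yes. The two arms are AASP plus usual care, and usual care alone. Only the first arm completes a plan, so a completion date can exist only for a participant in that arm.
2. **Who receives the date?** The Procedure section names the RAs at each site, in the plural, and does not restrict this to the RA who handles allocation. It could mean one responsible RA per site, but the text does not say so.
3. **Is any RA meant to be masked?** This is implied only. The Randomisation section singles out one RA as unblinded. No sentence says that other RAs or outcome assessors are masked.
4. **Do the recipients conduct the follow-up interviews?** This is not stated. It is likely, because the Harm section has RAs involved in checking for serious adverse events and discussing imminent risk with participants. It remains an inference.
5. **Does other text close the gap?** No. Research team members may deliver plans, and the article does not separate deliverers from assessors. RAs have access to the site files. At 6 months the SUS and CSQ-8 are given in one arm only, and Table 1 gives visits but not the order within a visit. If those measures, or an interview that discusses the AASP, came before the SITBI, the arm would be disclosed at that point.
6. **How many participants are affected?** This is unknown. With 90 randomised 1:1, the AASP arm holds about 90 / 2 = 45. That is a ceiling and not a count, because the notification sentence covers plans reported by support workers and the split between support workers and research team is not given.
7. **How large could the bias be?** The document has no input for this. As an illustration of the mechanism only, assume no true effect, a 50% self-harm rate in each arm, full elicitation in usual care and a fraction *e* elicited in the AASP arm. The false difference is 0.50 × (1 − *e*):
   - *e* = 0.95: 0.50 × 0.05 = 2.5 percentage points
   - *e* = 0.90: 0.50 × 0.10 = 5.0 points
   - *e* = 0.85: 0.50 × 0.15 = 7.5 points

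   For scale, take 35 per arm at endpoint (half of the 70 in Planned analysis) and the same assumed 50% rates. The 95% half-width for a difference is 1.96 × √(0.25/35 + 0.25/35) = 1.96 × 0.1195 = 0.234, or about 23 points. The assumed distortions are well inside the sampling uncertainty of this pilot. None of these values estimates what will happen in the trial.

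**The case against.** The strongest reply is that the article never promises masked assessment. Staff roles and the routing of messages are details that a condensed article may leave to the full protocol, and the phrase about RAs at each site can be read as one responsible person per site. A reader might infer that every RA is told the allocation, that these RAs are the documented follow-up interviewers, and that a formal blinding scheme is defeated. The article supports none of these three statements, and they are not asserted here. The order of measures within the 6-month visit is likewise silence and not an error.

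The consequence is also bounded. Planned analysis says that the trial is not powered for a difference in effectiveness, the SITBI is one of several secondary outcomes, and no progression or stop criterion uses it. Participants know their arm and report their own self-harm, so some reporting bias would remain even with perfectly masked interviewers.

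What the reply does not remove is the conflict between two sentences that are both in the text. One gives a role a label that implies masking elsewhere, and the other fixes an information flow that ignores the label. That is a stated rule and not an omission, and unlike disclosure by participants it is avoidable.

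**Conclusion.** The point holds as an inconsistency. The Randomisation section implies that RAs other than the one handling allocation are not told it, while the Procedure section sends arm-revealing dates to site RAs without that limit. The effect on outcome assessment is conditional: it arises only if RAs who receive the dates also conduct the 1-month or 6-month SITBI. This is likely but unwritten. If so, an implied safeguard is undermined for an interview outcome and for the exploratory comparison between arms.

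The size of any bias cannot be estimated from the document. The feasibility measures that decide progression do not depend on the SITBI, so the matter does not threaten the pilot's main purpose. It should still be corrected, because the correction is cheap and bears on the design of the definitive trial.

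**What to change.** 1. Amend the Procedure section so that support workers report completion dates only to the unblinded RA named under Randomisation. The record should be kept where the other RAs do not see it, since RAs have access to the site files.
2. At 6 months, complete the SITBI and SBQ-ASC before the SUS, the CSQ-8 and the acceptability interview.
3. Where existing staffing allows, do not have the person who delivered a participant's AASP conduct that participant's follow-up SITBI. The article does not give RA numbers per site, so a dedicated separate assessor at every site should not be relied on.
4. Have the assessor record at each follow-up whether they learned the arm, and report this by arm.
5. If assessment is meant to be open, say so plainly and interpret the between-arm SITBI comparison accordingly.

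The cost is a change of wording, one extra item on the follow-up form and minor RA scheduling. The unblinded RA's role already exists. The remaining limitation is that participants may still reveal their arm, and item 4 would show how often that happens.

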### Data collection and data management

Overall responsibility for data collection lies with the CI. Data collected on paper assessment tools will be entered onto a secure validated data management system at sites. A unique trial number is allocated at recruitment and will be used to identify participants on all paper assessment tools used throughout the duration of the study. No participant identifiable data will leave the study sites. The quality and retention of study data will be the responsibility of the CI. All study data will be retained in accordance with the latest directive on Good Clinical Practice (GCP; 2005/28/EC) and local policy. Staff involved in the conduct of the study, including PIs, Trial Management Group, and RAs, will have access to the site files. Clinical information shall not be released without the written permission of the participant, except as necessary for monitoring and auditing by the sponsor, its designee, regulatory authorities, or the research ethics committee. Secure anonymised electronic data will, however, be released to the research study analysts for analysis. The PI and site staff involved may not disclose of use for any purpose other than the performance of the study, any data, record, or other unpublished, confidential information disclosed to those individuals for the purpose of the study. Prior written agreement from the sponsor or its designee must be obtained for the disclosure of any said confidential information to other parties. Any requests to access the final trial dataset may be considered under the sponsor data-sharing policy.

### Planned analysis

This external pilot RCT is not powered to estimate a target difference in relative effectiveness but rather to address outcomes to estimate the parameters for a future definitive trial. For pilot studies, a sample size of around 70 participants at endpoint, randomised to treatment vs. treatment as usual, has been recommended to provide sufficient precision to estimate parameters for a full definitive study power calculation [36]; therefore, 90 participants will be recruited to account for drop out.

The feasibility and acceptability outcomes will be analysed using qualitative and descriptive statistics based on mean, standard deviation, median, and interquartile range for continuous data. Number of events and the corresponding percentages will be reported for categorical data. Thematic analysis will be conducted on qualitative feasibility and acceptability interview data. As this is a pilot trial, no formal sample size calculation was performed. However, generalised linear models with appropriate distribution for continuous and categorical data will be used to explore associations between the secondary outcomes and other factors including demographic data. A Bayesian model will be used to estimate the posterior probability that an association between an outcome and a confounder is not the same in the AASP intervention and the usual care groups. For example, if the posterior probability is greater than 60%, we would recommend that such factor is adjusted for a future definitive trial. The external pilot trial will also provide estimates of missing data, which will be calculated as the proportion of participants with outcome data. Using cross-tabulation, we would explore whether participants in the intervention group are more or equally likely to report missing outcome data than those in the usual care group. All data will be analysed under the intention to treat the principle; no interim and no sub-group analysis are planned.

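### The example rule for choosing adjustment covariates in the definitive trial tests effect modification, so it cannot tell a prognostic factor from an unrelated one

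*Protocol article*

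**What the plan says.** All of this is in the Planned analysis section of the protocol article.

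- Generalised linear models are to "explore associations between the secondary outcomes and other factors including demographic data". No adjustment recommendation is attached to them.
- A Bayesian model is then to give the "posterior probability that an association between an outcome and a confounder is not the same in the AASP intervention and the usual care groups".
- The decision attached to that probability, introduced as an example, is: "if the posterior probability is greater than 60%, we would recommend that such factor is adjusted for a future definitive trial".
- The design assumes "a sample size of around 70 participants at endpoint", and "90 participants will be recruited to account for drop out".

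The Randomisation section specifies 1:1 allocation without stratification. The Procedure section places the baseline measures before randomisation. Table 1 shows SITBI, SBQ-ASC and EQ-5D-5L collected at both baseline and 6 months.

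**The concern.** The criterion and the action do not match. A difference between arms in the outcome–factor association is effect modification. It answers whether the treatment effect varies with the factor. Whether to adjust is another question: it depends on how much outcome variance the factor explains on average over the arms. Calling the factor a confounder does not close the gap, because randomisation means that baseline factors do not systematically confound the treatment comparison.

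The pilot exists to supply parameters for a definitive trial. Covariate choice feeds the residual SD and hence the sample size of that trial. As an illustration with an assumed value, a baseline factor correlated 0.6 with the outcome in both arms explains 0.6² = 36% of the outcome variance, leaving a residual SD of √0.64 = 0.8 times the unadjusted one. The stated rule has no means of picking out such a factor.

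**Working it through.** **Inputs.** About 70 analysed (Planned analysis), 1:1 (Randomisation), so 70/2 = 35 per arm; threshold 60% (Planned analysis). The article gives no derivation for 60%, so there is no figure to reproduce. Prior, event definition and outcome distribution are not stated. I assume a continuous outcome with a standardised covariate, and vary the rest.

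**Step 1: why prognostic strength drops out.** Let the slopes be b_A and b_U, and the estimated difference d = b_A − b_U. If both true slopes equal b, then b cancels from d, and the posterior for the difference depends only on d and its standard error. Prognostic strength enters only through the residual SD, which affects the standard error. This does not depend on the prior or the threshold.

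**Step 2: flat prior, no true difference.** The posterior probability that the difference is positive is then uniform on 0 to 1 over repeated trials.

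- One pre-set direction: P(flag) = 1 − 0.6 = 0.40.
- Either direction: P(flag) = 2 × (1 − 0.6) = 0.80.

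**Step 3: simulation, n = 70, equal slopes in both arms, total outcome variance 1.** Entries are the percentage of runs flagged (6,000 runs; 20,000 for the two margin rows). The margin rows use a flat prior and the event that the absolute slope difference exceeds the margin.

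| Reading of the rule | Slope 0 | 0.3 | 0.5 | 0.7 |
|---|---|---|---|---|
| Flat prior, either direction | 79.9 | 80.0 | 79.9 | 79.7 |
| Flat prior, one direction | 39.1 | 40.4 | 40.0 | 39.1 |
| 50:50 point-null, slab SD 0.25 | 8.7 | 8.4 | 9.1 | 9.0 |
| 50:50 point-null, slab SD 0.5 | 8.3 | 7.8 | 7.4 | 6.4 |
| 50:50 point-null, slab SD 1.0 | 5.1 | 4.6 | 4.5 | 3.6 |
| Difference beyond margin 0.2 | 34.9 | 31.7 | 26.4 | 17.7 |
| Difference beyond margin 0.5 | 2.5 | 1.8 | 1.1 | 0.2 |
| *Contrast: main effect, two-sided p < 0.05* | 4.7 | 70.9 | 99.2 | 100 |

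Reading along each row, the rule's flag rate is flat or falls as the factor becomes more prognostic; the small rises are about one percentage point or less. Reading down, the level varies widely with the unstated prior and event definition. The last row shows only that data of this size do carry the relevant information; it is not proposed as a selection rule.

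**Step 4: what the rule does detect.** Take slopes of +0.25 and −0.25, a difference of 0.5 with average slope zero. Ordinary adjustment for such a factor gains nothing. It is flagged in 97% of runs under the flat prior (either direction) and in 52–61% under the 50:50 point-null priors, while the main-effect test picks it up in 5%.

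**The case against.** Several counter-arguments have weight.

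- **The rule is an advisory example.** It is introduced as an example and phrased as what the authors would recommend. It says if, not only if, so other routes to adjustment remain open. That stands: one cannot claim that a prognostic factor would be lost to the definitive trial, only that this rule would not identify it. But a different threshold would still be applied to the wrong quantity.
- **Prognostic associations are already to be explored.** The generalised linear models could supply them. That also stands, and makes the fix easy. What is missing is the link: the only stated recommendation rests on the interaction probability.
- **The prior and event definition may be in an analysis plan that is not shown.** This is fair, and it limits what can be said about noise. A reader might infer that the rule flags irrelevant factors at close to a coin-flip rate, or that every factor is flagged because two continuous slopes are never exactly equal. The article supports neither as a general statement: the first needs a flat or weak prior, the second a continuous prior with an exact-equality event. Under a 50:50 point-null prior an unrelated factor is flagged only about 3–9% of the time. No such detail, however, turns an interaction into a measure of prognosis.
- **Sub-group analysis.** A reader might see a contradiction with the statement that "no interim and no sub-group analysis are planned". That is arguable at best, since an exploratory interaction used for design advice need not count as a sub-group analysis. I do not rely on it.

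**Conclusion.** The stated criterion is the wrong one for its purpose. It measures effect modification and is used to recommend adjustment. For factors with equal slopes, its flag rate carries no useful information about prognostic strength under any of the readings examined, and Step 1 shows why no choice of prior or threshold would repair this.

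The rate for an unrelated factor is conditional: 40% (one pre-set direction) or 80% (either direction) with a flat prior, and about 3–9% with a 50:50 point-null prior. In the last case a strongly prognostic factor with equal slopes goes unflagged in about 91–97% of trials. These figures assume a continuous outcome, a linear model and about 35 per arm.

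Severity is moderate. The consequence is poor covariate advice for the later trial. The pilot's feasibility outcomes, progression and stop criteria, sample size and participant safety are untouched, so this should not be read as a threat to the pilot itself.

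**What to change.** Replace the Bayesian criterion as the basis for the adjustment recommendation, and attach that recommendation to the association models already planned:

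1. For each baseline factor, and always for the baseline value of the outcome where it is collected (SITBI, SBQ-ASC, EQ-5D-5L), estimate the association with the 6-month outcome across both arms, adjusted for arm.
2. Report the correlation or R-squared with a 95% interval, and the residual SD with and without the factor.
3. Recommend covariates on prognostic strength together with clinical knowledge, not on a single fixed cut-off. At n = 70 an observed correlation of 0.3 has a 95% interval of about 0.07 to 0.50 (Fisher transformation: 0.3095 ± 1.96/√67), so any one cut-off would be fragile.
4. If between-arm differences in association are still of interest, report them as exploratory interval estimates and do not use them to choose covariates.

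The cost is a rewrite of two sentences in the Planned analysis section. No extra data are needed, and the modelling is simpler.
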